# Protocol to evaluate the efficacy and safety of tolvaptan in patients with refractory ascites after liver resection: an open-label, single-arm phase I/II study

**DOI:** 10.1097/SP9.0000000000000015

**Published:** 2023-12-15

**Keywords:** hepatic resection, postoperative ascites, refractory ascites, tolvaptan

## Abstract

**Background::**

In patients with chronic liver diseases such as cirrhosis, massive ascites after hepatic resection is the cause of prolonged hospitalization and worsening prognosis. Recently, the efficacy of tolvaptan in refractory ascites has been reported; however, there are no reports on the efficacy or safety of tolvaptan for refractory ascites after hepatic resection. This study aims to evaluate the efficacy of early administration of tolvaptan in patients with refractory ascites after hepatic resection.

**Materials and methods::**

This is an open-label, single-arm phase I/II study. This study subject will comprise patients scheduled for hepatic resection of a liver tumor. Patients with refractory ascites after hepatic resection (drainage volume on postoperative day 1 ≥5 ml/body weight 1 kg/day) will be treated with tolvaptan. The primary endpoint will include the maximum change in body weight after hepatic resection relative to the preoperative baseline. The secondary endpoints will include drainage volume, abdominal circumference, urine output, postoperative complication rate (heart failure and respiratory failure), number of days required for postoperative weight gain because of ascites to decrease to preoperative weight, change in improvement of postoperative pleural effusion, total amount of albumin or fresh frozen plasma transfusion, type and amount of diuretics used, and postoperative hospitalization days.

**Conclusion::**

This trial will evaluate the efficacy and safety of tolvaptan prophylaxis for refractory ascites after hepatic resection. As there are no reports demonstrating the efficacy of tolvaptan prophylaxis for refractory ascites after hepatic resection, the authors expect that these findings will lead to future phase III trials and provide valuable indications for the selection of treatments for refractory postoperative ascites.

## Introduction

HighlightsMassive ascites after hepatic resection is the cause of prolonged hospitalization and worsening prognosis.No study has reported on the efficacy or safety of tolvaptan for refractory ascites after hepatic resection.This trial will evaluate the efficacy and safety of tolvaptan prophylaxis for refractory ascites after hepatic resection.These findings will lead to future phase III trials and provide valuable indications for the selection of treatments for refractory postoperative ascites.

Postoperative ascites is one of the most common complications after liver resection and is reported in 5–56% of patients with liver resection^1,2^. Despite advancements in perioperative management and patient selection, the incidence rate of postoperative ascites remains high. The reduction in functional liver tissue due to hepatic resection leads to postoperative sepsis, nutritional deprivation, and compromised immunity, which further aggravates liver function^3^. In addition, as several patients have chronic liver diseases, such as cirrhosis, postoperative deterioration of liver function and portal hypertension due to intraoperative manipulation can lead to a large accumulation of ascites^4–6^. Postoperative ascites accumulation requires prolonged hospitalization after hepatic resection due to prolonged drainage and infection. The continuous loss of large amounts of plasma in ascites can also lead to liver failure^7–9^, and the occurrence of postoperative ascites after liver resection increases the risk of long-term mortality^10^. Furthermore, patients with refractory ascites after liver resection are more expensive to treat due to prolonged hospitalization and albumin administration^8,11^.

Based on the clinical practice guidelines for liver cirrhosis published by the Japanese Society of Gastroenterology, spironolactone is the first choice for patients with frequent drainage after hepatic resection, and furosemide is used when the effect of spironolactone is unsatisfactory^12^. However, spironolactone is refractory in ~15–20% of patients with ascites and does not respond to diuretic therapies^13^. Additionally, the use of high doses of spironolactone causes renal function deterioration and mineral abnormalities^14^. Patients with refractory ascites can be treated with various therapies, including concentrated ascites reinfusion therapy, peritoneovenous shunting, and transjugular intrahepatic portosystemic shunting; however, their efficacy is limited^15–17^.

Recently, the efficacy of the additional use of tolvaptan in patients with cirrhosis has been demonstrated. In patients who do not respond to existing diuretic therapy, tolvaptan results in weight loss, ascites reduction, increased urine output, and improved symptoms related to edema in ~60% of patients^18–21^. Several studies have reported that tolvaptan use in patients with refractory ascites improves their long-term prognosis^22,23^. Furthermore, tolvaptan results in significantly lower renal dysfunction in patients with ascites effusions due to cirrhosis treated with tolvaptan compared with those not treated with tolvaptan^24,25^.

Tolvaptan is an orally selective vasopressin type 2 receptor antagonist that inhibits water reabsorption by decreasing aquaporin 2 expression in the collecting duct, thereby promoting free water excretion without increasing sodium excretion^26,27^. It has also been reported to maintain renal blood flow during diuresis without activating the renin-angiotensin-aldosterone system^28,29^. As tolvaptan can improve congestive symptoms without impairing renal function, its efficacy in patients with acute heart failure and complications after cardiac surgery is also attracting attention^30,31^.

For these reasons, we hypothesized that the prophylactic use of tolvaptan in patients with refractory ascites after hepatic resection would be effective in controlling ascites and protecting renal function. However, there are no reports regarding the efficacy of tolvaptan in patients with refractory postoperative ascites.

This study aims to determine whether tolvaptan can be used for the early control of refractory postoperative ascites. To the best of our knowledge, this is the first study to investigate the safety and efficacy of early tolvaptan in refractory ascites after hepatic resection, and valuable indications for the selection of treatments for refractory postoperative ascites.

## Methods/design

### Study design

This single center, open-label, single-arm phase I/II clinical study will evaluate the efficacy and safety of early ascites control using tolvaptan in patients with ascites effusion after hepatic resection. The primary endpoint of this study will be the maximum perioperative weight change. The study design is illustrated in Figure 1. The case registration period for this study is from March 2023 to December 2025. The study protocol was issued on 21 December 2022 and the amendment number is 1.0. This study protocol was approved by the Institutional Review Board of Hiroshima University, Japan (approval no. CRB2022-0018).

**Figure 1 F1:**
[figure not shown]
Study design.

### Study objectives and endpoints

The primary endpoint of this study will be the maximum change in body weight (BW) after hepatic resection relative to the preoperative baseline. We consider using drainage volume as the primary endpoint; however, drainage volume is highly variable and inaccurate. Weight change correlates well with drainage volume and has less variability; hence, we use weight change as the primary endpoint. The secondary endpoints will be the following: (1) drainage volume, (2) abdominal circumference, (3) urine output, (4) postoperative complication rate (heart failure and respiratory failure), (5) number of days required for postoperative weight gain because of ascites to decrease to preoperative weight, (6) change in improvement of postoperative pleural effusion, (7) total amount of albumin or fresh frozen plasm (FFP) transfusion, (8) type and amount of diuretics used, and (9) postoperative hospitalization days.

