### Sample size calculation

In a phase III clinical trial conducted by Sakaida *et al.*
^18^ on the efficacy of tolvaptan in patients with cirrhosis with hepatic edema, weight losses were –0.44 kg (SD, 1.93) in the placebo group (*n*=80) and –1.95 kg (SD, 1.77) in the tolvaptan group (*n*=82). In a dose-ranging study of tolvaptan in patients with cirrhosis with hepatic edema conducted by Okita *et al*.^19^ weight losses were –0.36 kg (SD, 2.06) in the placebo group (n=25) and –2.3 kg (SD, 2.35) in the tolvaptan group (n=25). In other words, 1–2 kg of weight loss is expected with tolvaptan.

In our previous data, a postoperative weight gain of ~3 kg was observed patients with refractory ascites who underwent drainage of 5 ml/BW 1 kg on the first day after hepatectomy. As the same weight and ascites loss as in previous literature are expected to occur, it is assumed that the use of tolvaptan can limit postoperative weight gain to 2 kg. Assuming an SD of 2.0, an effect size of 0.5, a power of 0.9, and a significance level of 0.1, 25 cases are required; considering that the dropout rate is ~10%, 30 cases are set as the required number of cases.

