#### Observation and examination schedule

Urine output, BW, and abdominal circumference will be measured daily until discharge. Preoperative BW should be measured within 7 days prior to surgery, and BW should be measured as soon as possible after waking up. Drainage volume should be measured daily until the drain is removed. The timing of the drain removal will be at the discretion of the attending physician. Blood tests will be performed daily until 7 days postoperatively, and after 10 days at the discretion of the attending physician. Preoperative blood tests should be performed within 90 days prior to surgery. Chest radiography will be performed within 90 days before surgery, immediately after surgery, and on first, third, fifth, and seventh postoperative days. CT will be performed according to the patient’s condition. After discharge, BW and abdominal circumference measurements, blood tests, and chest radiography will be performed during outpatient visits 30 and 90 days postoperatively. The patients will also be evaluated for adverse events. Observation will be completed 90 days postoperatively.

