As there are no reports demonstrating the efficacy of tolvaptan prophylaxis for refractory ascites after hepatic resection, we will analyze the safety and efficacy of this therapy in this clinical trial. We expect that these findings will lead to future phase III trials and provide valuable indications for the selection of treatments for refractory postoperative ascites.

This study protocol has several limitations. Firstly, it is a single-arm study, not a comparative study. Second, some confounding factors cannot be completely ruled out. Postoperative ascites may be influenced by the volume of resected liver, liver damage, and operative time. If positive results are obtained in this phase I/II study, we plan to conduct a phase III study including a control group to control for confounding factors. Within the limitations of this study, we believe that this study to evaluate the efficacy and safety of tolvaptan in patients with refractory ascites after hepatic resection is a useful tool that can lead to a phase III study.

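### Weight change is measured from a preoperative weight that includes the liver tissue later removed; this biases secondary endpoint (5), and the primary comparison only if specimen weights differ from the earlier patients'

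*Protocol article*

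**What the plan says.** Under Study objectives and endpoints, the protocol article defines the outcome: "The primary endpoint of this study will be the maximum change in body weight (BW) after hepatic resection relative to the preoperative baseline". The Observation and examination schedule fixes the reference: "Preoperative BW should be measured within 7 days prior to surgery". The reason given for using weight is that it stands in for drainage: "Weight change correlates well with drainage volume and has less variability; hence, we use weight change as the primary endpoint".

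Secondary endpoint (5) uses the same reference: "number of days required for postoperative weight gain because of ascites to decrease to preoperative weight".

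The benchmark is in Sample size calculation: "In our previous data, a postoperative weight gain of ~3 kg was observed patients with refractory ascites", with the expectation that "it is assumed that the use of tolvaptan can limit postoperative weight gain to 2 kg". The calculation then reads: "Assuming an SD of 2.0, an effect size of 0.5, a power of 0.9, and a significance level of 0.1, 25 cases are required".

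The Discussion mentions resected volume once, among the limitations: "Postoperative ascites may be influenced by the volume of resected liver, liver damage, and operative time". There it is an influence on ascites, not a part of the measured weight. The article does not describe subtracting the specimen, and it states no limit on the size of resection.

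**The concern.** Weight is chosen as a marker of retained fluid, yet between the baseline and every later weighing the surgeon removes solid tissue. That tissue is not fluid, so its loss is a systematic error in the marker. It always acts in the same direction: the heavier the specimen, the smaller the apparent gain.

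Two results depend on this. Endpoint (5) is meant to say when weight gained through ascites has gone, but a patient can be back at preoperative weight with retained fluid in place of the removed liver. The primary endpoint is a single-arm mean to be judged against a figure from earlier patients. If the two groups differ in how much liver was removed, that difference enters the result as if it were a drug effect, or hides one.

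**Working it through.** **Inputs from the protocol article (Sample size calculation).** Benchmark gain 3 kg; expected gain 2 kg; SD 2.0 kg; effect size 0.5; power 0.9; significance level 0.1, sidedness not stated; 25 cases before dropout.

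**Assumed input.** Specimen weight m. The document gives none, so a range is used.

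**1. The plan's own figure.** The article does not spell out the test; the calculation implies a one-sample comparison with 3 kg.

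- n = (SD × (z for alpha + z for power) / difference)².
- One-sided 0.10, power 0.90: (2.0 × (1.2816 + 1.2816) / 1)² = 26.3, so 27. This is within two patients of the stated 25.
- At n = 25 the power is Φ(1/2.0 × √25 − 1.2816) = Φ(1.218) = 0.89.

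The stated size is close enough to use this setting below.

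**2. What the weight change measures.** Let F(t) be the fluid gained by day t. Ignoring other non-fluid change, measured change = F(t) − m. Since m is the same on every postoperative day, the maximum shifts by the same amount: max[F(t) − m] = max F(t) − m.

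**3. Endpoint (5).** Return to preoperative weight means F(t) − m = 0, so F(t) = m. For assumed specimens of 0.1, 0.3 and 0.5 kg, about 0.1, 0.3 and 0.5 kg of fluid remain when the endpoint is met. No comparison group is involved, so nothing cancels. The error cannot be put into days, because the article gives no rate of weight loss.

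**4. Primary comparison.** Let d be the trial's mean specimen weight minus the earlier patients' mean. If both groups were weighed from the same kind of baseline, the observed difference from 3 kg is the true fluid difference plus d in the direction of benefit. With d = 0 the offset cancels, and neither n nor the error rates change. Otherwise, at n = 25 and SD 2.0:

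- False-positive rate = Φ(d/2.0 × 5 − z for alpha)
- Power = Φ((1 + d)/2.0 × 5 − z for alpha)

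| Assumed d (kg) | False-positive rate, one-sided 10% | Benefit tail of a two-sided 5% test (nominal 2.5%) | Power, one-sided 10% |
|---|---|---|---|
| −0.3 | 2.1% | 0.3% | 0.68 |
| −0.1 | 6.3% | 1.4% | 0.83 |
| 0 | 10% | 2.5% | 0.89 |
| +0.1 | 15% | 4.4% | 0.93 |
| +0.3 | 30% | 11.3% | 0.98 |

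Worked case, d = +0.3: Φ(0.75 − 1.2816) = Φ(−0.532) = 0.30. Worked case, d = −0.3: Φ(1.75 − 1.2816) = Φ(0.468) = 0.68. The two-sided 5% column is included because the Statistical analysis section names that level.

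**The case against.** The best defence is that the benchmark carries the same offset. The 3 kg comes from the site's own hepatectomy patients, identified by the same day 1 drainage criterion. They too lost a specimen, and the natural reading is that their gain was also counted from a preoperative weight. Nothing in the article suggests a different resection mix. This largely stands for the primary comparison: it leaves a risk that the article does not let a reader check, not a demonstrated bias.

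It follows that a whole specimen weight should not be set against the planned 1 kg. The specimen is an offset within each patient, while the 1 kg is a difference between two groups that probably both carry it.

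A reader might also infer from the Discussion that large resections produce more fluid and hide more of it. The sentence there gives neither direction nor strength, so this is plausible but not documented. A reader might add ascites emptied at operation to the removed mass. The article does not say that patients have ascites before surgery, and emptied ascites would be a real loss of fluid, so that extension is not supported.

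It can further be said that endpoint (5) is secondary, that other non-fluid weight changes and a baseline up to 7 days old blur the arithmetic, and that drainage volume, abdominal circumference, urine output and pleural effusion are also recorded. All fair. These points soften the size of the error in endpoint (5) but not its direction. Nor is this a detail to be left to an analysis plan: the article fixes the reference weight, and a specimen weight that is not recorded cannot be used later.

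**Conclusion.** The point holds as a measurement flaw with limited reach. Because the reference is weighed before resection, weight change understates retained fluid by the specimen weight. Endpoint (5) therefore tends to be reached too early, whatever the comparator, with residual fluid roughly equal to the specimen.

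For the primary endpoint, a reader might infer that the trial is biased towards showing a benefit. The document does not support that. The effect depends on the difference in mean specimen weight between trial and earlier patients, which may be zero or of either sign. Each kilogram of difference moves the result by a kilogram: an assumed 0.3 kg is 30% of the planned effect (0.3 / 1). Confidence is high in the mechanism and in the direction for endpoint (5), but low in any magnitude. The error rates rest on an assumed d, SD 2.0, n = 25, a normal approximation and a one-sample comparison with 3 kg.

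**What to change.** 1. Record the resected specimen weight for every patient.
2. Define endpoint (5) against preoperative weight minus specimen weight.
3. Prespecify a specimen-corrected version of the maximum weight change. Make it the primary version only if the 3 kg benchmark is re-derived with the same correction. Otherwise keep the uncorrected change as primary and report the corrected one as a sensitivity analysis.
4. State the baseline behind the 3 kg figure, and compare specimen weights in the trial and the earlier patients where they are available.

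The cost is one data field, one derived variable and a sentence in each endpoint definition. There are two downsides. Earlier patients may lack specimen weights; correcting the trial but not the benchmark would then raise the trial's gain against 3 kg and break the comparison, which is why step 3 is conditional. Corrected gains will also look slightly larger than the uncorrected ones, so both should be shown.

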### Statistical analysis

The primary objective of the study will be to determine the efficacy and safety of tolvaptan therapy. For items observed as continuous values, the number of examples, number of missing examples, mean (median), SD (quartile), and range (minimum-maximum) will be calculated as summary statistics. For items observed as discrete values, the number of examples in each category and their percentages will be calculated as summary statistics. For safety evaluation, the number and percentage of adverse events will be calculated using the subjects for whom at least one research treatment has been performed as the analysis population. Statistical tests for the main analysis will be performed at a 5% significance level (two-sided).

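### Days to return to preoperative weight is an interval-censored time to event, and the only summary the article states, for plain continuous values, does not suit it

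*Protocol article*

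**What the plan says.** Under *Study objectives and endpoints* the protocol article lists secondary endpoint "5) number of days required for postoperative weight gain because of ascites to decrease to preoperative weight". It gives no rule for a patient who has not returned to that weight.

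The section *Observation and examination schedule* fixes when weight is known:

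- In hospital: "Urine output, BW, and abdominal circumference will be measured daily until discharge".
- Afterwards: "After discharge, BW and abdominal circumference measurements, blood tests, and chest radiography will be performed during outpatient visits 30 and 90 days postoperatively".
- End of follow-up: "Observation will be completed 90 days postoperatively".

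Length of stay is itself an outcome, "9) postoperative hospitalization days", and no expected value is given for it.

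The section *Statistical analysis* states one rule for every continuous item: "For items observed as continuous values, the number of examples, number of missing examples, mean (median), SD (quartile), and range (minimum-maximum) will be calculated". The section names no time-to-event or censoring method and does not mention this endpoint by name.

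**The concern.** A number of days is a continuous item, so on a plain reading it falls under the generic summary. That summary needs one number per patient, and the weight schedule cannot supply one for everybody. A patient who goes home above preoperative weight must then be either left out as missing or given the date of the next visit. The two choices push the result in opposite directions.

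This is the only listed endpoint that measures how quickly weight returns to baseline, and the article intends positive results to lead to a controlled phase III study. With one open-label arm and 30 planned patients, the reported recovery time would depend partly on discharge practice and partly on a coding rule that could be chosen after the data are seen.

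**Working it through.** The article states no figure for this endpoint, so there is none to reproduce. Its sample-size calculation concerns the primary endpoint and plays no part here.

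**Step 1. What the schedule reveals.** Let T be the day of return and D the day of discharge, with D before day 30.

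| Patient's course | What is known about T |
|---|---|
| Returns in hospital, T ≤ D | Exact day |
| Above baseline at D, back by the day-30 visit | D < T ≤ 30 (interval-censored) |
| Above baseline at day 30, back by the day-90 visit | 30 < T ≤ 90 (interval-censored) |
| Still above baseline at day 90 | T > 90 (right-censored) |
| Lost or died earlier | T > last weight taken (right-censored) |

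The generic summary can use the first row as it stands. The other four rows must be dropped or turned into a single day.

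**Step 2. Direction of each handling.** Dropping rows 2 to 5 averages T given T ≤ D, which leaves out slow patients for any given length of stay, so the mean tends to be too low. Coding the visit replaces T by 30 or 90 in rows 2 and 3, and each replacement is at or above the true day, so the mean is too high.

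**Step 3. Size, on assumed inputs.** The documents give neither the distribution of T nor that of D, so both are assumptions:

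- T log-normal, median 10, 14 or 21 days, log-SD 0.5, rounded up to whole days.
- D log-normal, median 10, 14 or 21 days, log-SD 0.35, either independent of T or correlated 0.6 with it on the log scale.
- 400,000 simulated patients per setting.

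Check on the true mean: median × exp(0.5²/2), plus about 0.5 for rounding up. For median 14 this is 14 × 1.133 + 0.5 = 16.4 days, which agrees with the simulation.

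| Setting (median T, median D) | Returned in hospital | True mean | Mean, others dropped | Mean, visit day used |
|---|---|---|---|---|
| 10, 21, correlated | 97% | 11.8 | 11.4 | 12.3 |
| 14, 14, independent | 52% | 16.4 | 11.5 | 24.1 |
| 14, 14, correlated | 55% | 16.4 | 12.1 | 23.9 |
| 21, 10, correlated | 5% | 24.3 | 10.7 | 43.2 |

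The first and last rows are the extremes of the 18 settings run:

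- Others dropped: too low by 11.8 − 11.4 = 0.4 up to 24.3 − 10.7 = 13.6 days.
- Visit day used: too high by 12.3 − 11.8 = 0.5 up to 43.2 − 24.3 = 18.9 days.

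The sign was the same in all 18 settings under each handling. The median is not a reliable refuge: in both middle rows it is 11 days with others dropped and 19 days with visit dates, against a true 15. Where 97% return in hospital it is unaffected (10 days all three ways).

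**Step 4. A second shape.** With T Weibull (shape 1.5, median 12, mean 13.8 days) and D normal with mean 10, SD 3, floor 5 and independent of T, 41% return in hospital. Their mean is 6.0 days, and visit coding gives about 24. With mean discharge at day 14, 57% return in hospital, with mean 7.7 days. If discharge instead tracks recovery (D equal to T plus 0 to 2 days, SD 3), 59 to 79% return in hospital. Their mean is 12.2 to 13.2 days, a shortfall of (13.8 − 13.2)/13.8 = 4% to (13.8 − 12.2)/13.8 = 12%.

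**The case against.** The strongest reply is that handling of non-events for one of nine descriptive secondary endpoints belongs in an analysis plan or full protocol, neither of which is shown, and that the article does not rule out a Kaplan-Meier analysis. That limits the weight of the point but does not remove it. The article does state a summary for continuous items, and that summary does not fit this endpoint.

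Four stronger readings are tempting, and the documents do not support them.

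- **Discharge ends weight follow-up.** It does not. Weights at days 30 and 90 bound a later return, so right-censoring begins at day 90 or at earlier loss.
- **Patients not back at discharge will be counted as missing.** That is an inference from a generic sentence about reporting a missing count. No rule for these patients is written.
- **Recovery will look too fast.** This holds only if those patients are left out. Coding the visit day makes recovery look too slow.
- **Drainage volume suffers likewise,** because "Drainage volume should be measured daily until the drain is removed". The article nowhere says that daily means among patients still draining will be reported; a total per patient fits its wording equally well.

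It is also fair to say that the size rests on assumptions and shrinks if patients tend to go home as their weight recovers. The 4 to 12% shortfall above shows this, and it stands as a limit on the size under the first handling.

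**Conclusion.** The point holds. Given the article's own weight schedule, this endpoint is exact in hospital, interval-censored after discharge and right-censored at day 90 or at earlier loss, and a plain continuous summary distorts it under either obvious handling. The direction depends on a rule that the article does not fix, and the amount cannot be derived from the documents. The ranges above (0.4 to 13.6 days too fast, 0.5 to 18.9 days too slow) belong to the assumed distributions and are not predictions for this trial. The distortion is small if nearly everyone returns before discharge and large if few do. It affects the interpretation of one descriptive secondary endpoint and leaves the primary endpoint, maximum weight change, untouched. The change is worth making because it is cheap and the result is meant to inform a phase III study.

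**What to change.** In the section *Statistical analysis*, exempt this endpoint from the generic continuous summary and state that it is analysed as a time to event:

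- Estimate the median with a 95% confidence interval by a method for interval-censored data, using the discharge, day-30 and day-90 weights as interval limits. A Kaplan-Meier estimate is an acceptable simpler choice, but censoring at discharge would discard the later weights and assume that discharge is unrelated to recovery.
- Censor patients who have not returned at their last recorded weight.
- Report the number and proportion returned by discharge, by day 30 and by day 90.

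The scheduled weights suffice, so no new data are needed. The cost is slightly more programming and a wider interval than a plain mean and SD would suggest.
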